### Additional consent provisions for collection and use of participant data and biological specimens {26b}

On the consent form, participants will be asked if they agree to the use of their data should they choose to withdraw from the trial. This includes their data being used for analysis as well as any future publications or presentations related to the study. Since this is a monocenter trial, the consent form will not include a section regarding data sharing permissions. This trial does not involve collecting biological specimens for storage. All necessary measures will be taken to protect the privacy and confidentiality of participants. Participants will also be provided with the contact information for the study team in case they have any questions or concerns regarding their participation in the study.

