### Outcomes {12}

The primary outcome parameter is the overall opioid demand given as intravenous MME during the first 24 h after extubation.

Secondary outcome variables are the interval until extubation, ICU discharge, data collected in the ICU, length of hospital stay, the VAS at 2, 4, 6, 12, and 24 h after extubation, and the Overall Benefit of Analgesia Score (OBAS) at 24 h after extubation [12].

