### Participant timeline {13}

Demographic and baseline data such as age, weight, height, and ASA score are collected soon after informed consent is granted, usually the day before surgery. On the day of surgery, data that define the type of surgery and the type and size of central venous cannulation will be noted. Also, hemodynamic data such as arterial pressure, heart frequency, and blood oxygen saturation before and soon after the performance of the PECS block will be recorded. At the end of the surgery, the amount of opioids and sedatives used during the surgery will be noted. The time of ICU admission and hemodynamic data will be noted at ICU admission.

All opioids and other analgesics will be noted until the extubation and after 2, 4, 6, 8, 12, and 24 h. Also, the NRS score will be assessed at the defined time points.

After 24 h, the OBAS assessment will be performed, and the study participation will end.

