### Sample size {14}

The main hypothesis of this study is that the use of PECS II blockade in patients undergoing minimally invasive cardiac surgery reduces the overall opioid demand given as morphine milligram equivalents (MME) during the first 24 h after extubation. The sample size needed to test this hypothesis was based on four previous studies [15–18]. Study results were pooled and weighted due to considerable heterogeneity in variances. Assuming an average weighted effect size of 0.75 (Cohen’s *d*) aiming for a statistical power of 80% and a testing significance level of 5%, a sample size of 28 patients per group is required. Considering a potential dropout rate of 7%, we enrolled 60 patients (30 patients per group).

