### Methods in analysis to handle protocol non-adherence and any statistical forms to handle missing data {20c}

#### Per-protocol population

The per-protocol-population will include all patients who received intervention or sham intervention (placebo) and surgery without major protocol deviations. Significant protocol deviations or complications (hemodynamic instability, prolonged intubation, reintubation, bleeding, reoperation) and subsequent failure to obtain primary and secondary outcome data will be documented before the database lock.

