#### Intention-to-treat population

The intention-to-treat population will consist of all patients who were enrolled in the study and gave informed consent, but data is missing due to the abovementioned factors. This population will be analyzed in a separate ITT cohort. In case of withdrawals and missing data, the last observation carried forward (LOCF) procedure will be applied where appropriate.

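### Last observation carried forward is the only missing-data method named, it does not exempt the 24-hour opioid total, and it cannot give a valid value for that total

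*Protocol article*

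**What the plan says.** The section Outcomes {12} defines the endpoint as a sum over a fixed window: "The primary outcome parameter is the overall opioid demand given as intravenous MME during the first 24 h after extubation". The section Participant timeline {13} sets the recording times: "All opioids and other analgesics will be noted until the extubation and after 2, 4, 6, 8, 12, and 24 h". After extubation the recording intervals are therefore 2, 2, 2, 2, 4 and 12 h long.

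The section on the per-protocol population lists complications such as prolonged intubation, reintubation, bleeding and reoperation. It adds that "subsequent failure to obtain primary and secondary outcome data will be documented before the database lock", so missing primary data are expected.

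The section on the intention-to-treat population describes that set as enrolled, consenting patients, "but data is missing due to the abovementioned factors", and then gives the rule: "In case of withdrawals and missing data, the last observation carried forward (LOCF) procedure will be applied where appropriate". The article names no other method for missing data and no sensitivity analysis. It does not say whether the rule covers the MME total, or whether a running total or an interval dose would be carried.

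Two other sections bear on the remedy. Under the additional consent provisions {26b}, "participants will be asked if they agree to the use of their data should they choose to withdraw from the trial". Under the plans for outcome assessment {18a}, healthcare data come from the electronic patient file.

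**The concern.** LOCF takes the last recorded value as a stand-in for the value at the end of follow-up. A cumulative dose does not work that way: the running total at hour h is only the part of the 24 h total used so far. Carrying it forward amounts to assuming no opioid after hour h. The patients concerned include those with reintubation, bleeding or reoperation, and the article gives no reason to expect zero use in them.

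Carrying an interval dose does not solve the problem. A dose from a 2 h interval would stand in for a 4 h and a 12 h interval as well.

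The intention-to-treat estimate of the MME difference is at stake. With 30 patients per arm, a few badly imputed totals can move it, and the movement depends on which arm loses patients and when.

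**Working it through.** **Planned figures.** The section Sample size {14} gives Cohen's d = 0.75, 80% power, 5% significance, 28 per group, 7% dropout and 60 enrolled. With a two-sided test (assumed, as sidedness is not stated), n = 2(1.960 + 0.842)² / 0.75² = 27.9, so 28 per group is reproduced by the normal approximation. Planned loss is 60 − 56 = 4 patients.

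**Step 1: share of the true 24 h total credited, constant rate (assumption).** A carried running total gives h/24. A carried interval dose gives (h + last interval length × number of later intervals)/24.

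| Last seen (h) | Running total carried | Interval dose carried |
|---|---|---|
| 2 | 8% | (2 + 2×5)/24 = 50% |
| 4 | 17% | (4 + 2×4)/24 = 50% |
| 6 | 25% | (6 + 2×3)/24 = 50% |
| 8 | 33% | (8 + 2×2)/24 = 50% |
| 12 | 50% | (12 + 4×1)/24 = 67% |

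**Step 2: declining use, halving every 12 h (assumption), last seen at 6 h.** The cumulative share is F(h) = (1 − 2^(−h/12))/0.75, so F(4) = 0.275, F(6) = 0.391, and the 4–6 h dose is 0.1155 of the total.
- Running total carried: 39%.
- Interval dose carried into three later intervals: 0.391 + 3 × 0.1155 = 74%.
- Hourly rate carried over 18 h: 0.391 + 18 × 0.1155/2 = 143%.

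The result can be too low or too high, depending on what is carried.

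**Step 3: effect on the difference, running total carried.** Inputs: SD 1 in each arm, true difference 0.75, control mean 1/CV, 30 per arm, loss at 4 h (f = 4/24), constant rate. The article gives no MME mean or SD, so control CVs of 0.5 and 0.75 are assumptions. Each affected arm mean is multiplied by 1 − (k/30)(1 − f), where k is the number lost.
- Two lost per arm: 0.75 × (1 − (2/30)(5/6)) = 0.75 × 0.944 = 0.71. This does not depend on the CV.
- Four lost in the block arm, CV 0.5: 2 − 1.25 × 0.889 = 0.89. CV 0.75: 1.333 − 0.583 × 0.889 = 0.82 (0.815 before rounding).
- Four lost in the placebo arm, CV 0.5: 2 × 0.889 − 1.25 = 0.53. CV 0.75: 1.333 × 0.889 − 0.583 = 0.60.

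**Step 4: simulation of the same cases** (gamma totals, t-test, 20,000 runs).

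| Loss at 4 h | Power, CV 0.5 | Power, CV 0.75 |
|---|---|---|
| 2 per arm | 75% | 78% |
| 4 in block arm | 92% | 87% |
| 4 in placebo arm | 50% | 66% |

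With no true effect and all four losses in one arm, type I error is about 11% (CV 0.5) or 8% (CV 0.75). With two lost per arm it is 3% to 4%. For comparison, analysing only complete 24 h totals, when loss is unrelated to opioid need, gave about 0.75 SD, about 5% type I error and about 78% power.

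**The case against.** The strongest reply is that the rule applies only where appropriate, never names the primary outcome and does not say what is carried. A careful analyst might therefore never use it on the MME total. It is true that the text does not settle this. But it gives no criterion for the decision, names no alternative, and expects primary data to be missing, so the qualifier does not protect the endpoint.

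Exposure may also be small. Follow-up is 24 h in hospital, a study nurse reviews the files, and doses can be read from the electronic record. LOCF is attached to an intention-to-treat cohort that the article calls separate, without saying which population is primary. Patients never extubated have no post-extubation value to carry. All of this stands and limits the size of the problem.

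A reader might infer three stronger points that the documents do not support.
- *Imputed values always lower MME.* This is exact only for a carried running total, provided some opioid is used later. Step 2 shows that carrying the hourly rate can credit 143%.
- *The confidence interval is too narrow.* Take 2 of 30 patients in one arm, each credited with 25% of the total, and a true mean of 1. At CV 0.4 the standard error of the arm mean is 0.0785, against 0.0756 for 28 complete cases, so it is wider. At CV 0.8 it is 0.1455 against 0.1512, so it is narrower. The direction depends on an unknown CV.
- *The primary result is certain to be seriously biased.* The standard error of the difference is about √(2/30) = 0.26 SD. The balanced shift of 0.04 SD is small beside it, and the larger shifts need all four losses in one arm.

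The treatment of missing OBAS and the choice of model for VAS are side matters or preferences and are not part of this point.

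**Conclusion.** The concern holds in limited form. The article prescribes a method that does not suit a cumulative endpoint and leaves that endpoint within its reach. Neither reading of LOCF estimates the 24 h total: a carried running total imputes no later use, and a carried interval dose is wrong by an amount and in a direction set by the use profile.

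At the planned 7% loss, the intention-to-treat difference shrinks slightly if losses are balanced (0.75 to about 0.71 SD). If losses are one-sided, it moves either way (0.53 to 0.60 SD or 0.82 to 0.89 SD). These figures assume a running total is carried, a constant opioid rate, loss at 4 h and control CVs of 0.5 to 0.75. None of these is given in the article. The point should be fixed, but it does not by itself invalidate the trial.

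**What to change.** In the section on the intention-to-treat population, state that LOCF will not be applied to the 24 h MME total. Then set out, in order:

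1. For every randomised patient who agreed to data use, take the opioid doses actually given through 24 h after extubation from the electronic patient file, including after a complication or withdrawal.
2. For totals still incomplete, multiply impute the missing interval MME (0–2, 2–4, 4–6, 6–8, 8–12 and 12–24 h) from arm, earlier intervals and baseline variables such as age and weight, and sum to the 24 h total.
3. Add one simple sensitivity analysis, for example shifting the imputed values by arm until the conclusion changes.

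This should be settled before database lock and without knowledge of allocation. The sample size is unchanged and no new assessments are needed. The cost is a revised paragraph, some file review for the few patients affected, and a little more analysis work in R.

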### Plans to give access to the complete protocol, participant-level data, and statistical code {31c}

The entire protocol of the study will be published together with a manuscript on the clinical trial results. The datasets analyzed during the current study and the statistical code will be available from the corresponding author upon reasonable request. It will only be accessible to personnel directly involved in the study.

## Oversight and monitoring

### Composition of the coordinating center and trial steering committee {5d}

This is an investigator-initiated, single-center trial, run by a small study team that can be seen as the trial steering committee. Organizational support will be provided by the Competence Centre for Clinical Trials, Medical University of Innsbruck (KKS). The study team meets on a daily basis, to review routine clinical cases. Study-related topics will be discussed during this daily meeting as appropriate. The KKS will provide consultancy during the study initiation and closure phases, as well as on demand.

### Composition of the data monitoring committee, its role and reporting structure {21a}

An independent local monitor (Tirol Kliniken) will check trial quality repeatedly (at least every 6 months) and check at least 10% of the signed informed consent files (ICF). Complete data of the first five participants will be reviewed, including inclusion and exclusion criteria. The study has a low risk; therefore, there is no need for data safety monitoring board.

### Adverse event reporting and harms {22}

Although serious adverse events are not to be expected, the sponsor and the principal investigator will suspend the study if there is reasonable doubt that the continuation of the survey will compromise the safety and well-being of participants. In this case, the local ethics committee will be informed immediately, and the study will remain suspended pending a favorable decision from the local ethics committee.

Adverse events will be noted, and serious adverse events will also be reported to the local ethics committee.

### Frequency and plans for auditing trial conduct {23}

For quality assurance, monitoring audits will be performed. An independent local monitor will perform the monitoring.

Monitoring visits will be conducted to review study plan compliance, compare CRFs and individual patients’ medical records, perform an accounting of study material, and ensure that the study is conducted according to applicable regulatory requirements. CRF entries will be verified with source documentation. Monitoring visits will be performed repeatedly for at least all 6 months and check at least 10% of the signed ICFs.

### Plans for communicating significant protocol amendments to relevant parties (e.g., trial participants, ethical committees) {25}

After the protocol has been submitted to the ethics committee (EC), any substantial change will require a formal amendment. The amendment must be signed by all of the signatories to the original protocol. Once the study has started, amendments should be made only in exceptional cases. The ethics committees must be informed of all amendments. Approval must be sought for ethical aspects and obtained from the competent authorities*.*

### Dissemination plans {31a}

For all publications, the data protection of the subjects will be maintained. This includes a presentation at national and international conferences and publications in scientific journals. The study data are the property of the Medical University of Innsbruck. The data from the whole trial can be published separately. There are no publication restrictions, and the trial results will be accessible to the public.

## Discussion

This study will assess the opioid demand during the first 24 h after extubation following MICS. The available evidence on using local anesthetics in major cardiac surgery is scarce [19].

The secondary endpoints assess the evolution of VAS during the first 24 h, namely 2, 4, 6, 8, 12, and 24 h after extubation. Also, the OBAS after 24 h will be assessed, giving a more subjective evaluation of the analgesia and its subjective benefit [12]. Additional secondary endpoints will be the LOS, the time until extubation, and collected monitoring data.

Acute postoperative pain and the development of chronic pain are significant issues in cardiac surgery [5, 20, 21]. Poor postoperative pain management can lead to delayed ventilatory weaning, prolonged ICU stay, and prolonged LOS [1, 22]. For decades, opioid-based “balanced cardiac anesthesia techniques” were used to provide good analgesia and suppress sympathetic response during cardiac surgery. Apart from “classical” opioid-related side effects such as nausea, vomiting, sedation, and respiratory depression, the role of opioid-based anesthesia in developing the current opioid crisis in the USA is discussed [5].

With the upcoming less invasive surgical approaches, such as MICS, where two or three small thoracotomies replace open surgery access, an increased interest in ERAS pathways arose in cardiac surgery [3]. A multimodal analgesia that includes different concepts, such as regional anesthesia, can decrease opioid use and opioid-related side effects and may help reduce the length of ICU stay and LOS. Given the need for full heparinization, using neuraxial techniques or the paravertebral block (PVB) remains controversial.

Over the last decade, several ultrasound-guided truncal fascial plane blocks have been latter block has shown to provide good analgesia to the anterolateral chest wall for modified mastectomy, including axilla dissection and pectoral muscle resection [10, 18]. It is unsurprising that this block has also been used as a rescue maneuver for severe postoperative pain in cardiac surgery. It also seems to be a valuable tool for analgesia in the insertion of implantable cardioverter defibrillators (ICDs) [5, 23, 24].

Given the strict unilateral right approach of MICS, the PECS II block could be an exciting addition to multimodal analgesia. And as central venous catheters are usually placed on the right side, the ultrasound-guided PECS II block does not require further positioning, washing, and covering of the patient, thereby adding an essential advantage in time and logistics compared to other regional anesthesia techniques.

This study was designed to clarify if a PECS II block could efficiently reduce opioids in patients undergoing unilateral MICS. This study’s results may support anesthesiologists in choosing strategies for multimodal analgesia.

## Trial status

Protocol version 1.4, effective date: 21 January 2022. First patient first visit (FPFV): 08 February 2022. Currently, 36 of 50 participants are included, date: 11 October 2022. Last patient last visit (LPLV) is expected in April 2023.

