**Methods:**

In a single center, prospective, triple-blinded, two-group randomized trial, 60 patients undergoing elective, unilateral minimal invasive cardiac surgery will be randomized to receive a PECS II with 30 ml of ropivacaine 0.5% (intervention group) or sodium chloride 0.9% (placebo group). The primary outcome parameter is the overall opioid demand given as intravenous morphine milligram equivalents (MME) during the first 24 h after extubation. Secondary endpoints are the visual analog scale (VAS) 2, 4, 6, 8, 12, and 24 h after extubation, the Overall Benefit of Analgesia Score (OBAS) after 24 h, the interval until extubation, and intensive care unit (ICU) discharge within 24 h, as well as the length of hospital stay (LOS).

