## Methods: participants, interventions, and outcomes

### Study setting {9}

In this single-center prospective, triple-blinded, two-group, randomized trial, 60 patients will be recruited and randomly assigned to one of the two groups to test the effect of a PECS II block with ropivacaine 0.5% on the postoperative opioid demand (see Consolidated Standards of Reporting Trials flow diagram (CONSORT) [13] in Fig. 1). The scope of this trial is to improve perioperative pain management in patients undergoing minimally invasive cardiac surgery.

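### Enrolment is set at 60 in the abstract, study setting and sample-size section, but Trial status reports progress against 50; the two must be reconciled

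*Protocol article*

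**What the plan says.** Three places in the protocol article give a total of 60:

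- Abstract, Methods: "60 patients undergoing elective, unilateral minimal invasive cardiac surgery will be randomized".
- Study setting {9}: "60 patients will be recruited and randomly assigned to one of the two groups".
- Sample size {14}: "a sample size of 28 patients per group is required", followed by "Considering a potential dropout rate of 7%, we enrolled 60 patients (30 patients per group".

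The inputs in Sample size {14} are "Assuming an average weighted effect size of 0.75" (Cohen's d) and "aiming for a statistical power of 80% and a testing significance level of 5" per cent. Whether the test is one- or two-sided is not stated.

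One place gives a different total. Trial status reads "Currently, 36 of 50 participants are included, date: 11 October 2022". The same paragraph dates protocol version 1.4 to 21 January 2022 and the first patient to 8 February 2022, and forecasts the last visit for April 2023.

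**The concern.** In the status line, 50 can only be read as the number the site is recruiting towards. It conflicts with the 60 given elsewhere and is below the 56 evaluable patients that the sample-size section requires.

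The trial has a fixed sample, and Interim analyses {21b} rules out any interim look. The planned total is therefore its only stopping point, and recruitment was still open when the status line was written. With two totals in print, either ending is open to question. A trial that closes near 50 could look as if it stopped short. One that closes at 60 could look as if it was extended past its published target. If 50 were the true target, the trial would also fall short of its stated power.

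**Working it through.** **Inputs.** From Sample size {14}: d = 0.75, power 80%, significance level 5%, 28 per group, 7% dropout, 60 enrolled. From Sequence generation {16a}: 1:1 allocation. From Statistical methods {20a}: Student's t-test or a non-parametric equivalent. From Trial status: 36 included between 8 February and 11 October 2022, target 50, last visit April 2023.

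**Step 1. Reproduce the plan's figures.** Normal approximation, two-sided 5%:

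n per group = 2 × (1.96 + 0.8416)² / 0.75² = 27.9, so 28. This matches.

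A one-sided 5% test would need 22 (normal approximation) or 23 (t-test) per group. Only the two-sided test reproduces 28, so two-sided is the supported reading.

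Dropout: 28 × 1.07 = 29.96, so 30 per group and 60 in total. This also matches.

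**Step 2. Compare 50 with the requirement.** The requirement is 2 × 28 = 56 evaluable. Fifty enrolled gives 25 per group with no dropout. With 7% dropout, 50 × 0.93 = 46.5, or about 23 per group.

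**Step 3. Power at each size.** The normal approximation uses power = Φ(0.75 × √(n/2) − 1.96). For n = 25, 0.75 × 3.536 − 1.96 = 0.692, and Φ(0.692) = 75.5%. The t-test column uses the noncentral t distribution. Both assume d = 0.75 and two-sided 5%.

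| Per group | Situation | Normal approximation | t-test |
|---|---|---|---|
| 30 | 60 enrolled, all evaluable | 82.8% | 81.5% |
| 28 | stated requirement | 80.1% | 78.7% |
| 25 | 50 enrolled, no dropout | 75.5% | 73.8% |
| 23 | 50 enrolled, 7% dropout | 72.0% | 70.1% |

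The comparison should be made within a column. From 28 per group, the loss is 80.1 − 75.5 = 4.6 to 80.1 − 72.0 = 8.1 points by normal approximation, and 78.7 − 73.8 = 4.9 to 78.7 − 70.1 = 8.6 points by t-test.

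**Step 4. Which total fits the timeline?** From 8 February to 11 October 2022 is 245 days, so accrual is 36 / 245 = 0.147 per day. At that rate:

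- 50 needs 14 more patients, 14 / 0.147 ≈ 95 days, reached in mid-January 2023.
- 60 needs 24 more patients, 24 / 0.147 ≈ 163 days, reached in late March 2023.

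Participant timeline {13} ends participation 24 hours after extubation, so the last visit should follow the last inclusion closely. April 2023 fits 60 better than 50.

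**The case against.** The strongest reply is that 50 is a typing error in a short status note. Three sections give 60, including the one that derives the sample size, and the accrual projection agrees with them. This largely stands, and it is why the power loss should not be presented as a property of the trial. It does not remove the need for correction: slower accrual could also carry a target of 50 into April, and nothing in the article says which number the site is working to.

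A reader might infer that the target was cut during recruitment, perhaps in response to data. The documents do not support that. No interim analysis is planned, version 1.4 predates the first patient, no change of target is described, and the section on protocol amendments {25} requires a formal amendment for any substantial change.

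A reader might also infer that the 60 is itself too small, because an exact t-test needs 28.9, so 29, per group, and 60 × 0.93 = 55.8 falls just under 56. These are rounding differences. The stated 28 follows from the standard formula, and 60 enrolled gives 81.5% by t-test if all are evaluable. The plan also allows non-parametric and regression analyses, so exact t-test power is not uniquely the planned power.

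Finally, the unstated sidedness matters to the figures: a one-sided 5% t-test would keep about 80% to 83% power with 50 enrolled. That reading does not reproduce 28 per group, so it is not a convincing defence of 50.

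**Conclusion.** The inconsistency is real: 60 in three sections, 50 in Trial status, with no explanation. Fifty is 6 short of the 56 evaluable patients required before any dropout. The likelier explanation is a slip for 60, but that rests on constant accrual and on the forecast last visit, and the article does not confirm it.

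It would go too far to conclude that the trial is underpowered. The drop to about 70–74% by t-test (72.0–75.5% by normal approximation) arises only if 50 is the true stopping point. It also assumes d = 0.75, equal groups and a two-sided 5% test. Nor should the t-test figures for 50 be set against the plan's 80%, which is the normal-approximation value; that adds between one and two points to the apparent loss. The derivation of 28 and 60 is acceptable as it stands.

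**What to change.** State one enrolment target throughout.

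- **If 60 stands:** change Trial status to 36 of 60. Leave the sample-size section and its 80% power as they are. The cost is one number in the text.
- **If 50 is the real target:** record the change and its reason in a dated amendment, and bring the abstract, Study setting {9} and Sample size {14} into line. Restate power for d = 0.75 at two-sided 5%, naming the method: about 74% with no dropout and 70% with 7% dropout by t-test (78.7% at 28 per group), or 75.5% and 72.0% by normal approximation (80.1% at 28 per group). The cost is an amendment and a lower declared power.

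In either case, stating that the 5% level is two-sided would remove the need to infer it.
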